## Abstract

**Background:**

Post-stroke aphasia (PSA) is one of the most devastating symptoms after stroke, yet limited treatment options are available. Prolonged intermittent theta burst stimulation (piTBS) is a promising therapy for PSA. However, its efficacy remains unclear. Therefore, we aim to investigate the efficacy of piTBS over the left supplementary motor area (SMA) in improving language function for PSA patients and further explore the mechanism of language recovery.

**Methods:**

This is a randomized, double-blinded, sham-controlled trial. A total of 30 PSA patients will be randomly allocated to receive either piTBS stimulation or sham stimulation for 15 sessions over a period of 3 weeks. The primary outcome is the Western Aphasia Battery Revised (WAB-R) changes after treatment. The secondary outcomes include The Stroke and Aphasia Quality of Life Scale (SAQOL-39 g), resting-state electroencephalogram (resting-state EEG), Event-related potentials (ERP), brain derived neurotrophic factor (BDNF). These outcome measures are assessed before treatment, after treatment, and at 4-weeks follow up. This study was registered in Chinese Clinical Trial Registry (No. ChiCTR23000203238).

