### Study design

2.1

This is a randomized, double-blinded, sham-controlled trial. The study will adhere to the ethical principles outlined in the Declaration of Helsinki and will follow the Consolidated Standards of Reporting Trials (CONSORT) guidelines (38), as well as the Recommendations for Interventional Trials (SPIRIT) (39). All patients who meet the inclusion and exclusion criteria will be randomly assigned in a 1:1 ratio to the following piTBS group and sham group after obtaining written informed consent. All patients will undergo corresponding assessments before treatment (T0), after treatment (T1), as well as during the 4-weeks follow up (T2). Please refer to Figure 1 and Table 1 for the specific study process. This study has been approved by the Medical Ethics Committee of the China Rehabilitation Research Center (No.2023-027-2) and registered in the Chinese Clinical Trial Registry (No. ChiCTR2300074533).

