**Figure 1 fig1:**
[figure not shown]
Flow chart of study procedure. EEG, electroencephalogram; T0, before treatment; T1, after treatment; T2, at 4-weeks follow up; a, Western Aphasia Battery Revised; b, The Stroke and Aphasia Quality of Life Scale; c, The Edinburgh Handedness Inventory; d, The National Institutes of Health Stroke Scale.

**Table 1 tab1:** Study process schedule.

	Pre-enrollment	T0	Intervention	T1	T2
	−7 days	Day 0		±3 days	±3 days
Screening	√				
Informed consent	√				
Random allocation		√			
Demographic information		√			
EHI		√			
NIHSS		√			
SAQOL-39 g		√		√	√
WAB-R		√		√	√
Resting-state EEG		√		√	
ERP		√		√	
Blood		√		√	
Adverse event			√	√	

T0, before treatment; T1, after treatment; T2, at 4-weeks follow up.

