#### Neurochemical assessment

2.5.3

To investigate serum biomarkers related to synaptic plasticity and neuronal excitability, 5 mL blood samples will be collected from patients before and after treatment. Then those blood promptly centrifuged at 3,000 r/min for a duration of 10 min to facilitating serum separation. The resultant serum is aliquoted and preserved at −80°C for further analyses.

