### Data analysis

2.6

All data will be analyzed by professional statisticians using SPSS software (Version 25.0; IBM, Armonk, NY, United States). Baseline characteristics will be described using means ± standard deviations for continuous variables and frequencies for categorical variables. Prior to applying independent sample t-tests or Mann–Whitney U tests for continuous variables, a normality test will be conducted using either the Kolmogorov–Smirnov or Shapiro–Wilk test. Categorical variables will be compared using chi-square tests or Fisher’s exact tests. The primary outcome is the change in WAB-R scores before and after treatment. The secondary outcomes include changes in blood markers, EEG, and ERP indices before and after treatment. These measures will be analyzed using a Linear Mixed Effects Model (LMM), where group acts as a fixed effect, time points as a repeated measure, and patients as random effects within the LMM framework. If significant interaction effects between groups and time points are revealed by the LMM, post-hoc comparisons will be conducted to identify the time points at which differences occur, using methods like Bonferroni-corrected pairwise comparisons.

The acquired EEG signals will be analyzed using MATLAB2021b. The EEGLAB toolbox (version 2023.0) will be used for EEG data preprocessing (51). MMN and N400 components in the ERP data will be extracted through time-window analysis and peak detection techniques. EEG data analysis will focus on power spectral analysis to assess changes in key EEG frequency bands, such as alpha and beta bands (52). These data will be analyzed within the LMM framework to examine the patterns of change before and after treatment and their correlation with clinical improvement. If the LMM reveals significant interaction effects between groups and time points, appropriate post-hoc comparisons, such as Bonferroni-corrected pairwise comparisons, will be conducted to identify the specific time points at which differences occur.

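### The abstract puts EEG, ERP and BDNF at follow-up but Table 1 does not; section 2.6 omits SAQOL-39 g and applies a multi-visit post-hoc step to two-visit measures

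*Protocol article*

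**What the plan says.** **Abstract, Methods.** After the primary outcome, WAB-R, it continues: "The secondary outcomes include The Stroke and Aphasia Quality of Life Scale (SAQOL-39 g), resting-state electroencephalogram (resting-state EEG), Event-related potentials (ERP), brain derived neurotrophic factor". The next sentence reads "These outcome measures are assessed before treatment, after treatment, and at 4-weeks follow up" and makes no exception for any measure.

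**Section 2.1 and Table 1.** The design section names T0, T1 and T2 in general terms and sends the reader to Figure 1 and Table 1 for detail. Table 1 ("Study process schedule") ticks WAB-R and SAQOL-39 g at all three visits. Resting-state EEG, ERP and blood are ticked at T0 and T1, and T2 is blank.

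**Section 2.5.3.** "5 mL blood samples will be collected from patients before and after treatment".

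**Section 2.6.** "The secondary outcomes include changes in blood markers, EEG, and ERP indices before and after treatment". The sentence that follows assigns a linear mixed model to the measures just listed. SAQOL-39 g is not named anywhere in the section. If the group-by-time interaction is significant, Bonferroni-corrected pairwise comparisons are to show at which visits the differences lie. This step is stated once for the outcomes in general and again for EEG and ERP.

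**The concern.** Three statements in one article do not fit together.

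1. **Visits.** A reader of the abstract expects EEG, ERP and BDNF data four weeks after treatment. The schedule does not collect them. If the abstract is the true intent, staff working from Table 1 will miss T2 measurements that cannot be recovered later.
2. **Outcome list.** SAQOL-39 g is a secondary outcome in the abstract and is collected at every visit, but the section that assigns the model lists a different set.
3. **Analysis step.** A search for the visits at which groups differ suits a measure with several post-baseline visits. On the Table 1 schedule, EEG, ERP and BDNF have one.

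The mechanism of recovery is a stated aim of the trial, so it matters how far in time the mechanism data reach and which single contrast carries the conclusion.

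**Working it through.** **Step 1: visits and analysis, side by side**

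| Outcome | Visits, abstract | Visits, Table 1 | Named in section 2.6 |
|---|---|---|---|
| WAB-R | 3 | 3 | yes (primary) |
| SAQOL-39 g | 3 | 3 | no |
| Resting-state EEG | 3 | 2 | yes |
| ERP | 3 | 2 | yes |
| Blood / BDNF | 3 | 2 | yes |

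The abstract names four secondary outcomes and section 2.6 names three.

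**Step 2: is a blank T2 cell only a table-reading fault?** Unlikely. The WAB-R and SAQOL-39 g rows of the same table do show T2 ticks, and section 2.5.3 independently limits blood to two draws. Section 2.6 also describes blood, EEG and ERP in before/after terms. That is weaker support, because it uses the same terms for WAB-R, which does have a T2 visit.

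**Step 3: planned counts.** With 30 patients and no dropout, each of EEG, ERP and blood has 30 × 3 = 90 measurements under the abstract and 30 × 2 = 60 under Table 1. The difference is 30 per measure, all at T2. SAQOL-39 g has 30 × 3 = 90 planned forms. These are maxima; the sample-size section expects about 10% dropout or exclusion.

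**Step 4: what the interaction test is with two visits.** With two groups and two visits, the group-by-time term has (2 − 1) × (2 − 1) = 1 degree of freedom. With complete data it is the between-group difference in mean T0-to-T1 change. Four simple comparisons could still follow it:

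- groups at T0, which compares randomised groups before treatment;
- T0 against T1 within each group (two tests), neither of which compares treatments;
- groups at T1, the only one of the four that bears on the treatment effect.

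**Step 5: precision of one baseline-adjusted comparison at T1.** Let n be the number per group, σ the standard deviation at each visit (assumed equal) and ρ the T0–T1 correlation. The documents give no ρ.

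- Difference in change: variance = 2 × 2σ²(1 − ρ)/n = 4σ²(1 − ρ)/n.
- Baseline-adjusted difference at T1: variance ≈ 2σ²(1 − ρ²)/n.
- Ratio = (1 − ρ²) / [2(1 − ρ)] = (1 + ρ)/2.

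| Assumed ρ | Variance ratio, adjusted to change |
|---|---|
| 0.3 | 0.65 |
| 0.5 | 0.75 |
| 0.7 | 0.85 |

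The ratio does not exceed 1. It is a large-sample result: estimating the baseline slope costs one degree of freedom, so with about 30 patients the gain can vanish when ρ is close to 1.

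**The case against.** The strongest reply is that the body of the article is coherent. Section 2.1 defers to Table 1, and Table 1 agrees with section 2.5.3 and with the wording of section 2.6. One compressed sentence in the abstract is the outlier, and staff who follow the Methods would not be misled. This stands: if Table 1 is what is intended, the visit conflict is a correction to the abstract.

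On SAQOL-39 g, section 2.6 introduces its list in terms that need not be exhaustive, and a model for each secondary outcome may be set out in an analysis plan that is not shown. A reader might infer that the scale could be reported or dropped once results are known. The documents do not support that. It is publicly named as a secondary outcome, described in section 2.5.1.2 and scheduled at every visit, so its absence from a report would be visible. What remains is a mismatch between two lists, and a model sentence that attaches to the list without SAQOL-39 g. Nor is it the only measure that patients rate: the tolerability questionnaire in section 2.5.1.5 also records subjective symptoms.

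On the post-hoc step, a reader might infer that with two visits there is nothing left to test. That is too strong. Finding that groups differ at T1 and not at T0 is a possible result of simple-effect comparisons, and section 2.6 makes the step conditional on a significant interaction. The step is poorly matched and largely redundant, not invalid.

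Finally, the two-visit mixed model already provides a valid between-group test of change. The baseline-adjusted comparison is an improvement in precision and clarity; it does not repair an invalid test.

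**Conclusion.** The point holds as an inconsistency with a limited consequence for analysis. Three secondary measures have three visits in the abstract and two in the schedule; one secondary outcome is missing from the list to which section 2.6 attaches its model; and the general post-hoc step adds little for measures with one post-baseline visit. For those measures a single adjusted comparison at T1 uses data already planned. Its variance is (1 + ρ)/2 times that of the change contrast, or 0.65 to 0.85 for assumed correlations of 0.3 to 0.7, given equal variances at both visits and complete data.

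Nothing here touches the primary outcome's visits: WAB-R is at T0, T1 and T2 in both the abstract and Table 1. The counts in the working measure the size of the discrepancy; they are not evidence of bias or of lost power. A reader might also infer that the registry entry carries the same error. The entry is not available, so that cannot be concluded.

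**What to change.** 1. **Reconcile the visits.** If Table 1 is right, the abstract could read: WAB-R and SAQOL-39 g are assessed at T0, T1 and T2; resting-state EEG, ERP and BDNF are assessed at T0 and T1. If T2 measurement of EEG, ERP and BDNF is intended, correct Table 1 and sections 2.5.3 and 2.6 instead.
2. **Name SAQOL-39 g in section 2.6** as a secondary outcome, with the same three-visit model as WAB-R.
3. **For EEG, ERP and BDNF on the two-visit schedule**, replace the interaction and post-hoc sequence with one comparison per index: the T1 value regressed on group and the T0 value, reporting the adjusted group difference with its 95% confidence interval. Limit mechanism claims to the end of treatment.
4. **Check the registry entry** against the reconciled text, and change it only if it differs.

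On the Table 1 schedule this costs wording changes and one simpler model, with no added visits or samples. If T2 measurement is intended, the cost is up to 30 further EEG recordings, 30 ERP recordings and 30 blood samples. The multi-visit model would then be appropriate for those measures.

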**Discussion:**

This study protocol is promising for improving language in PSA patients. Resting-state EEG, ERP, and blood examination can be used to explore the neural mechanisms of PSA treatment with piTBS.

**Clinical trial registration:**

https://www.chictr.org.cn/index.html, ChiCTR2300074533.

## Introduction

1

Stroke is the second leading cause of death and a major cause of disability worldwide (1). Aphasia is a functional impairment after a stroke that affects almost one-third of stroke survivors for acute and rehabilitation settings (2). Post-stroke aphasia (PSA) has a significant effect on patients including social interactions, depression, and lower quality of life (3–6). PSA treatment strategies include behavioral intervention, pharmaceutical interventions, noninvasive brain stimulation (7). Conventional speech and language therapy (SLT) is the mainstay of treatment, but the efficacy of SLT is not as good as it should be (8–10). And there is no consistent evidence that any medication has substantial effect on aphasia recovery (11). Non-invasive brain stimulation therapy has attracted increasing attention as a complementary treatment for PSA (12).

By generating induced electrical currents through the magnetic field that passes through the skull, transcranial magnetic stimulation (TMS) affects the excitability of the cerebral cortex (13). Intermittent theta burst stimulation (iTBS), a specific modality of TMS, offers the advantage of rapid administration and can be well-tolerated, making it a feasible intervention for stroke recovery (14–16). And it has shown to be promising in modulating cortical excitability and inducing neuroplastic changes in specific brain regions involved in language processing (17). Previous studies have consistently shown that iTBS is a valuable treatment modality for enhancing language function and inducing cortical plasticity in human brain networks over the short- and intermediate-term (15, 18). However, it is important to note that the degree of improvement in language scores has been relatively modest, and certain clinical trials have reported improvement limited to specific aspects, such as comprehension (19). Therefore, there is an urgent need to improve the overall therapeutic efficacy of iTBS in PSA. Possible reasons affecting treatment efficacy include dose and target of stimulation.

Most iTBS studies have used 600 pulses (18, 20), but study showed that increasing iTBS stimulation dose resulted in dose-dependent effects at the local level (cortical excitability) (21). The effect of three consecutive 600 pulses iTBS, named prolonged iTBS (piTBS), on cortical excitability was the most significant (21). Therefore, piTBS has also attracted much attention in recent years. For example, a study comparing different doses and modes of theta burst stimulation for refractory depression founded that piTBS were effective in improving depressive symptoms (22). Significant improvements were also seen in veterans with mild alcohol use disorder (23).

Another important factor affecting efficacy is the stimulation target. Classical language centers include Broca’s and Wernicke’s areas and their homologs in the right hemisphere continue to dominate the selection of target locations for TMS treatment of aphasia (18, 19, 24). Therapeutic efficacy based on these target targets remains limited. The supplementary motor area (SMA) has been neglected in speech and language processing, but recent research has shown that it has a superior control function during speech communication and language reception (25, 26). And it is particularly important when task demands increase, including a functional division of labor between different subregions in speech motor and cognitive processing (27). It has also been shown that PSA patients have reduced spontaneous brain activity in the left SMA (28). Transcranial alternating current stimulation on SMA targets significantly improves language comprehension (29). To date, there are no studies related to piTBS treatment based on SMA target.

Furthermore, the mechanism of piTBS to promote language recovery is not clear. Electroencephalogram (EEG) can be used to obtain temporal information on speech production, thus revealing the internal processing of language and compensating for the limitations of behavioral testing (30). The N400 is an electrophysiological indicator related to semantic processing. Compared to healthy controls and individuals with other types of brain damage, PSA patients typically exhibit diminished or absent amplitudes, prolonged latency, and irregular scalp distribution (31, 32). In a picture-text matching task, they reported an abnormal shift of the centro-parietal N400 waveform from the right hemisphere to the more lateral left hemisphere after treatment (33). The mismatch negativity (MMN), as an electrophysiologic index related to attentional and perceptual processing, has also been widely used in the assessment of PSA. Researchers founded an increase in MMN amplitude after treatment, which could confirm changes in neuroplasticity at the structural and lexical level, correlating with improvements in clinical symptoms in PSA patients (34). Abnormalities in the above two components are suggestive of their difficulties in processing and comprehending semantic information. Further studies will help to explore the electrophysiologic characteristics in PSA.

As a neuronal modulator, brain-derived nerve growth factor (BDNF) has been shown to be an important upstream regulator of hippocampal and neocortical long-term potentiation (LTP) during motor learning (35). BDNF can also be modulated by therapeutic interventions, with BDNF levels almost tripling in subjects receiving TMS compared to healthy subjects receiving sham stimulation (36). In addition, BDNF is increased in depressed patients who receive multiple TMS treatments (37). Therefore, we hypothesized that similar manifestations would be seen in PSA and that piTBS might alter the level of BDNF, which plays an important role in aphasia recovery.

In conclusion, this study aims to investigate the efficacy of piTBS targeting the left SMA in PSA patients, and to explore the underlying mechanisms facilitating language recovery. Through this study, we hope to provide new treatment strategies for clinical practice.

## Methods

2

### Study design

2.1

This is a randomized, double-blinded, sham-controlled trial. The study will adhere to the ethical principles outlined in the Declaration of Helsinki and will follow the Consolidated Standards of Reporting Trials (CONSORT) guidelines (38), as well as the Recommendations for Interventional Trials (SPIRIT) (39). All patients who meet the inclusion and exclusion criteria will be randomly assigned in a 1:1 ratio to the following piTBS group and sham group after obtaining written informed consent. All patients will undergo corresponding assessments before treatment (T0), after treatment (T1), as well as during the 4-weeks follow up (T2). Please refer to Figure 1 and Table 1 for the specific study process. This study has been approved by the Medical Ethics Committee of the China Rehabilitation Research Center (No.2023-027-2) and registered in the Chinese Clinical Trial Registry (No. ChiCTR2300074533).

**Figure 1 fig1:**
[figure not shown]
Flow chart of study procedure. EEG, electroencephalogram; T0, before treatment; T1, after treatment; T2, at 4-weeks follow up; a, Western Aphasia Battery Revised; b, The Stroke and Aphasia Quality of Life Scale; c, The Edinburgh Handedness Inventory; d, The National Institutes of Health Stroke Scale.

**Table 1 tab1:** Study process schedule.

	Pre-enrollment	T0	Intervention	T1	T2
	−7 days	Day 0		±3 days	±3 days
Screening	√				
Informed consent	√				
Random allocation		√			
Demographic information		√			
EHI		√			
NIHSS		√			
SAQOL-39 g		√		√	√
WAB-R		√		√	√
Resting-state EEG		√		√	
ERP		√		√	
Blood		√		√	
Adverse event			√	√	

T0, before treatment; T1, after treatment; T2, at 4-weeks follow up.

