#### Withdrawal criteria

2.2.3

Severe adverse reactions or complications, such as persistent headaches, seizures, or other discomfort related to TMS;Protocol violations: Patients unable to comply with the study protocol, such as refuse to undergo assessments or interruption of treatment for more than 3 consecutive days;Development of new health issues or worsening of existing conditions deemed inappropriate for continued participation in the trial;Use of other TMS or TES treatments;Withdrawal from the trial without any specific reason.

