#### Sample size

2.2.4

Based on the preliminary experimental results, the effect size [f(V)] for the piTBS group compared to the sham group in the primary outcomes is 0.25. With a significance level (α) of 0.05 and a power (1-β) of 0.95, considering a two-group design involving before and after treatment, and during follow-up assessments conducted at three time points, the anticipated sample size calculated using G*Power 3.1.9.7 for the repeated measures ANOVA model was 28. Anticipating a dropout/exclusion rate of around 10%, a total of 30 patients will need to be enrolled, with 15 patients allocated to each group.

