##### Tolerability and safety

2.5.1.5

This study will use a 16-item symptom questionnaire to rate the subjective symptom [headache, scalp pain, arm/hand pain, other pain(s), numbness/tingling, other sensation(s), weakness, loss of dexterity, vision/hearing change(s), ear ringing, nausea/vomiting, appetite loss, rash, skin change(s) or any other symptom(s)] on a scale of 0 to 5 (none, minimal, mild, moderate, marked, severe) prior to any TMS application (47). Assessments will be made at the end of each treatment session to detect the presence of any adverse events.

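### The visit schedule has no adverse-event assessment at T2, so harms between T1 and T2 are not systematically collected although every patient is assessed at T2

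*Protocol article*

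**What the plan says.** Three places in the protocol article fix when harms are looked for.

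- **Table 1, section 2.1 (Study design).** The row "Adverse event" is ticked under Intervention and under T1. Its T2 cell is empty. The table's footnote defines the last column as "T2, at 4-weeks follow up". The WAB-R and SAQOL-39 g rows are ticked at T0, T1 and T2.
- **Section 2.5.1.5 (Tolerability and safety).** A 16-item symptom questionnaire scored 0 to 5 is given before any TMS. The section then adds: "Assessments will be made at the end of each treatment session to detect the presence of any adverse events". It mentions no assessment after the treatment course.
- **Section 2.2.3 (Withdrawal criteria).** The harms the protocol expects appear as reasons for withdrawal: "Severe adverse reactions or complications, such as persistent headaches, seizures, or other discomfort related to TMS". A further criterion covers new or worsening health problems. Neither sets a time at which such events are asked about.

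The visits themselves apply to everyone. Section 2.1 states: "All patients will undergo corresponding assessments before treatment (T0), after treatment (T1), as well as during the 4-weeks follow up (T2"). Treatment is given "for 15 sessions over a period of 3 weeks" (Abstract, Methods).

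**The concern.** The follow-up periods for benefit and harm do not match. Language and quality of life are measured up to T2, but scheduled safety assessment ends at T1. The trial could report an effect 4 weeks after treatment without harms data collected in the same way over the same period.

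Three features of this trial make the gap worth closing.

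- The protocol itself lists persistent headache among the reactions it expects. Whether a headache persists or resolves once stimulation has ended cannot be learned from a schedule that stops at T1.
- Every participant has aphasia (WAB-R aphasia quotient below 93.8, section 2.2.1). Such patients are poorly placed to volunteer a complaint, so asking in a structured way matters more than usual.
- A new health problem between T1 and T2 could affect the T2 WAB-R score or lead to a missed visit. Without a question at T2, the trial may not be able to tell.

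**Working it through.** The plan states no figure on this point to reproduce. The check is a reading of the schedule, followed by a day count.

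**1. Is the empty cell real?** Other rows of the same table (WAB-R, SAQOL-39 g) keep their T2 ticks, so the T2 column was not lost when the text was read from the PDF. Section 2.5.1.5 independently places adverse-event assessment at treatment sessions. The Abstract takes its listed outcome measures to the 4-week follow-up, but adverse events are not in that list. Table and text agree: nothing is scheduled after T1.

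**2. How long is the gap?** Inputs:

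- Treatment: 3 weeks = 21 days (Abstract, Methods).
- Follow-up: 4 weeks = 28 days. The article does not say what the 4 weeks are counted from; the end of treatment is assumed.
- Visit window: ±3 days at T1 and T2 (Table 1).

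Time from first stimulation to T2: 21 + 28 = 49 days.

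| Case | Days from T1 to T2 | Share of time from first stimulation to T2 |
|---|---|---|
| T1 at end of treatment, T2 on its nominal date | 28 | 28/49 = 57% |
| T1 3 days late, T2 on its nominal date | 28 − 3 = 25 | 25/49 = 51% |
| T1 3 days late, T2 3 days early | 25 − 3 = 22 | 22/46 = 48% |
| T1 at end of treatment, T2 3 days late | 28 + 3 = 31 | 31/52 = 60% |

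The first two rows are the main range. The last two show that the T2 window does not change the picture.

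**3. Could late events plausibly occur at all in a trial this small?** The article gives no rate, so the rates below are assumptions. The treated arm has 15 patients: "with 15 patients allocated to each group". For an assumed per-patient rate p of an event between T1 and T2, the chance of at least one in the piTBS arm is 1 − (1 − p)^15.

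| Assumed p | Chance of at least one late event in 15 |
|---|---|
| 1% | 1 − 0.99^15 = 14% |
| 5% | 1 − 0.95^15 = 54% |
| 10% | 1 − 0.90^15 = 79% |
| 20% | 1 − 0.80^15 = 96% |

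The result depends wholly on p. It shows only that late events are not negligible by default.

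**4. After the change.** With adverse events assessed at T2 and asked about since T1, scheduled coverage rises from about 21 of 49 days (24 of 49 if T1 is 3 days late) to the whole period. Sample size, power and alpha do not change.

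**The case against.** The strongest reply is that nothing here is contradictory. Table 1 and section 2.5.1.5 fit together, the article never says that later events are ignored, and a condensed article commonly leaves unsolicited and serious event reporting to the full protocol. Safety is not among the outcomes in the Abstract or in section 2.6, and no claim of freedom from late harm is made.

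Much of this stands, and it limits the point in four ways.

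- **A reader might infer that every event after T1 is lost.** The article does not support that. Patients remain in the trial until T2, and the withdrawal criteria are not ended at T1, so a seizure or a new illness could still reach the team by spontaneous report or withdrawal. What is absent is a scheduled, solicited assessment.
- **A reader might take 57% as the share of harm missed.** It is a share of days. It would equal a share of harm only if the hazard were constant over the seven weeks, which nothing in the article says.
- **A reader might bring in the upper confidence bound for zero events among 15 patients.** That bound comes from the arm size and is the same with or without an assessment at T2, so it does not measure this gap.
- **A reader might assume that T2 is in person.** That is likely because the WAB-R is administered, but the mode of the visit is not stated.

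The appeal to a fuller document does not remove the point. Section 2.1 refers the reader to Table 1 for the study process, and that table fixes the assessments visit by visit. An analysis plan cannot recover answers to questions that the schedule does not ask.

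**Conclusion.** The point holds as a limited weakness of the data-collection schedule. Adverse events are assessed during treatment and at T1 but not at T2, although all patients are assessed at T2 for other measures. About 25 to 28 of 49 days (51% to 57%) pass without a scheduled safety assessment, on the assumption that T2 is 28 days after the end of 21 days of treatment. T1 is itself a post-treatment visit, so events in the first days after the last session may be caught there.

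The schedule is the same in both arms, and the primary outcome, randomisation, power and alpha are untouched. The consequence is confined to what can be said about harms after T1: as scheduled, the trial will have no systematic data on them. The change is worth making because it is cheap, not because the trial's main result is at risk.

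**What to change.** 1. In Table 1, tick the adverse-event row at T2.
2. In section 2.5.1.5, add that at T2 the same 16-item, 0–5 symptom questionnaire is given in both arms, together with a question on any event since T1, including seizures and new or persisting headache.
3. Report harms by arm for T0–T1 and T1–T2 separately, so that the treatment and follow-up periods can be told apart.

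The cost is a few minutes per patient at a visit that already takes place, one table cell, one or two sentences of text and an extra line in the safety table. It needs no new visit or instrument and no change to the sample size or the efficacy analysis.
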